### Process evaluation

In addition to the household survey, a comprehensive process evaluation, informed by the socio-ecological model, will be conducted before and after CCG construction (Figure 2).

#### Individual level

##### Semi-structured interviews

A purposive maximum variation sample of 60 households representing varying distance from the Greenway, and individuals of a range of age, gender and socio-economic position (SEP) will be selected and invited to participate in detailed semi-structured interviews. Participants will be identified from respondents to the household survey. The interviews will explore the effects of key determinants on physical activity behaviour. Specific topics will include (i) perceptions of own health, its determinants and lifestyle behaviours, (ii) perceptions of the barriers and facilitators to healthy lifestyles, (iii) effects of local environment on behaviours, motivation and personal health, (iv) knowledge of the Greenway and related local health promotion initiatives, and (v) perceptions of the quality of the local environment, including safety issues and expectations from the urban regeneration. The same participants will be interviewed at two time points, pre and post CCG construction. The qualitative data emerging from this series of interviews will add richly to the explanatory power of our quantitative data [35].

#### Community level

##### Focus groups

Physical activity intervention design and implementation can benefit from meaningful participation of the community and relevant agencies. Focus groups (n=14) will be conducted with community stakeholders utilising the networks and knowledge of local community agencies. This collaborative approach will facilitate purposive sampling to recruit adults for the focus group discussions representing the diverse population of the study area (e.g. age, gender, SEP). Topics explored will include engagement in physical activity, barriers and facilitators to physical activity in the local area, views on local facilities and opportunities for physical activity and the perceived usefulness of the proposed Greenway to encourage local residents to be more active. Focus groups will be audio-recorded and data will be analysed using a mixture of text-based content analysis and thematic analysis [36,37].

#### Organisational level

##### Network analysis

The sustainability of any efforts to support behaviour change at both individual and organisational levels will depend on the strength and empowerment of the community and inter-organisational networks. An assessment of the processes that facilitate or inhibit the effective implementation of the intervention strategy will form an integral part of the overall design [38]. The evolution of community capacity and the effectiveness of these partnerships to meet their health promotion objectives will be assessed before and after the CCG construction period using established partnership and social network analysis tools and techniques [39,40]. Briefly, the strength and extent of network ties between the statutory and voluntary CCG stakeholders, in terms of reciprocal relationships, trust, exchange of information, technical assistance, referrals or funding, will be evaluated using a range of mathematical parameters describing the network. This includes the network density, degree and between-ness centrality, which reflect respectively the connectedness of the network by the proportion of possible ties in a network that are present, the number of ties to and from a stakeholder (used to determine opinion leaders), and the frequency that one lies between others thus occupying a strategic position on the network [41]. The evolution of these measures over the duration of the CCG construction will be an important dimension of the outcome evaluation. This will be complemented by semi-structured interviews with key CCG stakeholders, including local health professionals, employers, retailers and activists from voluntary and statutory bodies, to evaluate the impact of the Greenway on the effectiveness of the partnership and on knowledge mobilisation. All qualitative proceedings will be audio-recorded and analyzed using a form of thematic analysis [36] whereby the identified themes and sub-themes will be represented in terms of a matrix for further analysis [37].

#### Built environment

##### Geographic information systems (GIS)

In order to examine the specific influence of changes to the built environment, GIS data of the environmental features in the area at the finest available spatial level (varying from address of the individual household to Super Output Area level) pre- and post-regeneration will be collected. This will include mapping of the footpath network (“Real Walkable Network”) across the study area, topography, transport features, physical activity opportunities, for example, green space, local amenities, parks, using a mix of aerial photography, and checked using open source spatial data and aerial photography. The network will be tested and validated by peer checking of mapped elements and ground-truthing (observational checks) to assure its quality. The development and validation of the Real Walkable Network will be the subject of a future publication. These data will be used to revise the “walkability index” for a 500 m and 1000 m buffer zone around the household of each respondent to the household survey. Analysis will include an assessment of the changes in walkability of the neighbourhoods and the influence of distance decay (exposure to the regeneration project) on physical activity behaviour. We will also map and describe individual household level change in objectively measured accessibility to the regenerated, environmental physical activity opportunities and examine the association between change to the built environment and change in physical activity and other health-related outcomes.

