### Overall research design

The PARC Study is a before-and-after evaluation of the effects of the CCG on physical activity and health, and comprises of four main elements:

1. A quasi-experimental before-and-after survey of the CCG population (repeated cross-sectional design), utilising data from a parallel Northern Ireland-wide survey for comparison;

2. Assessment of change in the local built environment and walkability using geographic information systems (GIS);

3. Semi-structured interviews with 60 residents, and a range of community stakeholders before and after the regeneration project;

4. A cost-effectiveness evaluation.

The study has been approved by the Office for Research Ethics Committees, Northern Ireland (09/NIR02/66).

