#### Summative evaluation

##### Survey design

A survey of a random selection of households will be conducted before-and-after the regeneration of the CCG. The target area was selected as 29 electoral wards identified during the development of the CCG project (Figure 1). The sampling strategy will ensure proportionality with the Northern Ireland population based on estimates of the number of residents aged 16 or older provided by the 2001 Census. The surveys will each take place over a 12-month period and a random probability sampling framework will be constructed by a random selection of addresses from each of the selected output areas using the Royal Mail’s Postal Address File (PAF), stratified by the proportion of the overall population within each area. An information sheet about the study will be posted to each household, which will be followed up by a visit approximately 1-2 weeks later from a trained interviewer. If no one is present at the time of interview, up to five call-backs will be made in order to achieve a completed interview. If no response to call backs, the address will be recorded and another address within the same area will be selected from the PAF using the same selection process. For each household, the ‘last birthday rule’ (person in the household aged 16 years and over who had the most recent birthday) will be applied to randomly select an individual aged 16 years and over within each selected household to complete the survey. After the individual has given written consent to participate, an interviewer-administered questionnaire will be completed.

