**Figure 2 F2:**
[figure not shown]
**Overview of the evaluation framework informed by the socio**-**ecological model ****(adapted from Sallis et al 2012 **[51]**).**

Outcomes which may moderate/mediate the relationship between changes in the built environment and physical activity will be assessed. These include (i) perceptions of the characteristics of the environment associated with active travel and physical activity, including aesthetics, safety and walkability [16] - a “walkability index” for each Super Output Area will be created (based on land use characteristics and street connectivity [17,18]) using GIS, to explore the relationship between high and low “walkable” environments and physical activity; (ii) self-rated health using the EQ-5D-3L instrument [19,20]; (iii) health related quality of life using the Short-Form 8 Health Survey (SF-8) [21]; (iv) mental well-being using the Warwick-Edinburgh Mental Well-being Scale [22,23]; (v) common core theoretical constructs such as intention, stage of change, self-efficacy and outcome expectancy based on the outcomes from the 2001 NIH sponsored workshop and studies to develop a unified theory of behaviour change applied to physical activity [24,25]; (vi) items relating to neighbourhood social capital, as reflected in civic engagement, neighbourliness, social networks and support, and perceptions of the local area using the instrument employed in the UK General Household Survey [26,27]; (vii) awareness of the Greenway, assessed using items similar to those employed in an evaluation of the VERB campaign [28] - this will be used to assess the possible mediating effects of social marketing activities to promote physical activity in the CCG area; (viii) individual socio-demographic variables including age, gender, marital status, housing tenure, educational attainment, household income level and employment status. Access to a bicycle and the number of vehicles available for use by the household will also be recorded. In addition, using a tailored questionnaire, a range of discrete choice questions will assess preferences for physical activity with reference to the local built environment, amenities and transport infrastructure [29].

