##### Sample size and analyses

The sample size was estimated using the same method as Cochrane et al. [32], based on Cohen’s arcsine transformation [33]. We estimated the initial population proportions of those achieving the recommended levels of physical activity using alternative assumptions of 20%, 30% and 50%. Therefore the sample size required to detect differences in population proportions is 934 at both time points, assuming an effect size of 0.15 at 90% power (α = 0.05). We will survey 950 individuals who reside in the electoral wards whose geographic centroid is within one mile of the CCG area, before and after the intervention. In addition, we will survey a further 289 individuals who reside in other wards in the wider area (representing a similar proportion of the population to the other areas), which will allow us to explore distance decay. Since the “comparator” community survey undertaken by SportNI will involve approximately 4,000 individuals across Northern Ireland, we will essentially have a large control group providing additional power to demonstrate any differences that might emerge in the CCG population.

Area-by-category classifications of change in the proportion of the population meeting the physical activity guidelines will be compared by cross-tabulation and the difference in distributions assessed for statistical significance using the χ^2^ test. Multinomial logistic regression will be used to test a prediction model for categories of change in physical activity by area/age/income bracket, allowing a comparison of odds ratios for the various categories of physical activity by area [34]. A key strength of the analysis will be the capacity to make multiple comparisons between the CCG area and similar groups and areas across Northern Ireland as well as the capacity to analyse trends in physical activity behaviours according to distance between respondents’ homes and the Greenway.

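### The survey observes no respondent's or household's change in activity, so the change-on-change analyses do not fit the design, and the distance analysis names no contrast that removes pre-existing differences

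*Protocol article*

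**What the plan says.** **Design.** Overall research design in the protocol article lists as its first element "A quasi-experimental before-and-after survey of the CCG population (repeated cross-sectional design"). Under Survey design, "a random probability sampling framework will be constructed by a random selection of addresses from each of the selected output areas", and the last-birthday rule is then used "to randomly select an individual aged 16 years and over within each selected household to complete the survey". No re-contact of first-wave respondents or addresses is described for the survey.

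**Built-environment analysis.** The GIS section collects spatial data before and after regeneration. It will map "individual household level change in objectively measured accessibility to the regenerated, environmental physical activity opportunities" and then "examine the association between change to the built environment and change in physical activity and other health-related outcomes". It also names distance decay as a measure of exposure to the project.

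**Statistical section.** Sample size and analyses proposes a multinomial logistic regression whose outcome is the category of change in activity, with area, age and income bracket as predictors. It counts as a key strength "the capacity to analyse trends in physical activity behaviours according to distance between" homes and the Greenway. The 289 respondents from the outer wards are there to explore distance decay.

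**Walkability unit.** Under Survey outcome measures, a walkability index "for each Super Output Area will be created". The GIS section revises it "for a 500 m and 1000 m buffer zone around the household of each respondent".

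**The concern.** A regression of change on change needs both changes for each unit of analysis. Change in accessibility can be had for any address, because the GIS data exist for both periods. Change in activity cannot, because the two waves interview different people at different addresses. The multinomial model has the same difficulty: a respondent seen once has an activity category but no category of change.

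The distance analysis raises a second problem. The wards differ before any building starts: The intervention section puts seven of them in the most deprived quarter of Northern Ireland. The document does not say whether deprivation follows distance from the Greenway. If activity already varied with distance, a gradient by distance would carry that difference unless it is compared between waves, and the text names no such comparison.

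At stake is the built-environment part of objective (ii) and the main quantitative exposure-response evidence within the study area. The primary outcome, a change in a population proportion, needs no paired data and is not affected.

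**Working it through.** **1. The plan's own figure.** Inputs from Sample size and analyses: h = 0.15, power 90%, α = 0.05. With the arcsine method and a two-sided test,

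n per wave = 2 × ((1.960 + 1.282)/0.15)² = 933.99, so 934.

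The stated 934 is reproduced (a one-sided test would give 762). From baselines of 20%, 30% and 50%, h = 0.15 is a rise of 6.3, 7.1 and 7.5 percentage points. This calculation covers the simple before-and-after comparison, not a contrast by distance.

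**2. Paired activity data in the survey.** Treat the 950 inner respondents in each wave as random draws from about 87,500 residents (The intervention). Expected overlap = 950 × 950 / 87,500 ≈ 10 people. Even a redrawn address need not give the same adult, because of the last-birthday rule.

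**3. What a distance comparison without differencing would do (illustration).** Assume 30% active near the Greenway and 35% in the outer wards, with no effect. These proportions are assumptions; the documents give none by distance.

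- Difference on the arcsine scale: 2·asin(√0.35) − 2·asin(√0.30) = 0.107
- SE for 950 v 289 in one wave: √(1/950 + 1/289) = 0.0672
- Ratio: 0.107/0.0672 = 1.59, nominally significant about 36% of the time

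**4. Precision of the contrast that removes fixed differences.** Assume 289 outer respondents in each wave (the text does not say this outright), simple random sampling and no clustering.

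- SE = √(2/950 + 2/289) = 0.0950
- Power at h = 0.15: Φ(0.15/0.0950 − 1.96) = Φ(−0.38) ≈ 35%
- Detectable h at 90% power: 3.242 × 0.0950 = 0.31, or about 14 to 15 percentage points from baselines of 20% to 50%
- Detectable h at 80% power: 0.27

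Splitting the 950 inner respondents at the median distance gives SE = √(4/475) = 0.0918 and about 37% power. For context, the difference in change between 950 Greenway respondents and 4,000 Northern Ireland respondents per wave has SE = √(2/950 + 2/4000) = 0.0510 and about 84% power.

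**The case against.** Several points on the other side have force.

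- **Valid analyses exist without a panel.** A reader might infer that the built-environment analyses are impossible, or bound to be confounded, because respondents are not followed. The documents do not support that. GIS data for both periods and located homes in both waves allow a wave-by-exposure interaction, or change on change at area level. Both remove fixed differences under parallel trends. This objection stands.
- **Household level is attached to accessibility.** The phrase in the GIS section qualifies accessibility, which can be computed. The clause on change in activity gives no unit, and the section allows spatial levels from household to Super Output Area. This stands, so the unit for activity has to be stated rather than withdrawn. The multinomial outcome is the plainer mismatch, although the same sentence goes on to speak of odds ratios for categories of activity, so activity status may have been meant.
- **The distance analysis is not described as post-only.** Trends within a before-and-after survey may well mean change over time by distance. The text does not settle this, so step 3 shows a risk and not the planned analysis.
- **Walkability units.** A reader might infer that an area index before would be subtracted from a buffer index after. Nothing says so, and revising the index may simply refine it. What remains is a request to fix one unit for both periods.
- **The accelerometer sub-study may hold paired data.** It has 100 residents at both time points, but the text does not say outright that they are the same people. It is small, and its stated purpose is comparison with the questionnaire.
- **Model detail belongs in the analysis plan.** That is fair for covariates and model form. It does not cover an outcome that the stated design cannot supply.
- **Already exploratory.** The plan does say that the 289 serve to explore distance decay. That covers part of the labelling, but not the limited precision.

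**Conclusion.** The point holds in a limited form. The stated design does not observe change in activity for survey respondents or households, so the analyses worded as change in activity cannot be run at that level. The distance analysis names no contrast that would separate a Greenway effect from earlier differences by distance. Both can be repaired with data already planned.

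The repaired contrast is weak: about 35% power at h = 0.15, against 90% for the simple before-and-after comparison. The 35% is indicative only. It takes 289 outer respondents in each wave, borrows the effect size set for another comparison, and splits distance in two, so a continuous-distance model could differ. Clustering within areas would lower it.

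The interaction also rests on parallel trends across distance and on a stable population. Turnover is a live threat: the protocol itself plans to monitor tenancy turnover (Other data).

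**What to change.** 1. Compute pre- and post-regeneration accessibility and walkability on the same 500 m and 1000 m buffers for every sampled address in both waves.
2. Replace the change-on-change, category-of-change and distance-trend wording with a pooled two-wave model of activity status (1,239 per wave if the 289 are recruited each time). Include wave, exposure (network distance, or change in accessibility at that address) and wave by exposure. Name the interaction as the exposure-response estimate. Area-level change on change by Super Output Area is an alternative.
3. State the parallel-trends and stable-population assumptions.
4. Report the result as exploratory, with confidence intervals, and acknowledge its limited precision.

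Cost: extra GIS processing for both sets of addresses and changes to the analysis text; no new survey data. The price is a less precise estimate and a more modest conclusion on the built environment.

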##### Usage of the greenway

Direct observation of usage of the Greenway will be conducted in two ways: (i) conducting before-and-after Intercept Surveys of CCG use (at four locations on the Greenway), adapting SUSTRANS methodology; (ii) employing the SOPARC (System for Observing Play and Recreation in Communities) methodology, a validated technique to assess the use being made of green space and parks in the area before and after the construction of the CCG [42]. We will recruit volunteers from the local community, who will undertake a period of training, to help with data collection at eight target areas using the SOPARC protocol, over the course of seven days, both in winter and summer. These data will be complemented by assessing the quality of built environment features using a validated instrument, Environmental Assessment of Public Recreation Spaces (EAPRS) [43]. Analysis will explore the characteristics of Greenway users, the types of activities they are involved in and the relationship between parks/green space use and environmental quality.

Further, effective mechanisms are in place to collect information to assess the reach, ‘dose’ and fidelity of intervention implementation and of the resources used. The Belfast Health and Social Care Trust and the East Belfast Community Development Agency will collect core data on the number of people enrolling and completing various physical activity promotion initiatives in the CCG area.

##### Other data

During the construction of the Greenway, aspects of local or regional transport infrastructure and policy may change, with implications for the active travel behaviour of local residents. Changes will be monitored using routinely available information, including bus timetables and traffic survey data collated by the Department for Regional Development (DRD). The latter will yield comparative information on average annual distances travelled by all forms of transport and access to and use made of public transport. DRD also collects routine information on bicycle use via electronic monitors dispersed throughout the city. In addition, effects on road traffic accidents will be monitored using routinely available statistics, compiled by the Police Service of Northern Ireland (PSNI). The effect of the urban regeneration on tenancy turnover rates, the quality of local social housing stock, and crime statistics in the target area and in neighbouring areas will also be monitored using Northern Ireland Housing Executive and PSNI data respectively.

